### Control group

Children in the control schools will receive treatment as usual according to prevailing guidelines for school health services [33] and in addition parents receive the 12-page health information brochure (component 1 of the intervention). Usual treatment means a visit of the child accompanied by parents to the school nurse soon after the child begins school for a discussion regarding the school situation, the child’s overall well-being, relations with friends, possible health and learning problems, and diet and physical activity. The child’s height and weight is measured and eyesight and hearing are tested. If a child is overweight or obese, the guidelines for school health services state that the child should be met with an empathic approach with focus on improvement of health behaviours rather than on weight as such. No detailed instructions are given. The curriculum in pre-school class prescribes that pupils should be provided with opportunities to experience different forms of physical activity, and to develop an understanding of how health is affected and can be promoted in various ways [51].

### Outcome evaluation

All questionnaires are filled in via the project website (www.enfriskskolstartplus.se) with personal accounts for each family. The website has been developed by the research team in collaboration with IT consultants. One member of the research team is appointed administrator of the website. For parents who cannot or do not want to use the website, paper versions will also be available. In order to increase the response rate to the questionnaires, weekly reminders are sent out via e-mail and text messages. Parents are also offered support to log in to the website and if problems arise when responding to the questionnaires.

All outcomes are assessed as the difference between the intervention and the control group directly after the end of intervention at 6-months post baseline, and at follow-up 18 months post baseline, adjusted for baseline values. All outcome and mediator variables, indicators, instruments used and time points of assessment are listed in Table 3.

**Table 3 Tab3:** Overview of outcome and mediator variables, indicators, instruments and time points of assessment

Variables	Indicators and instruments	Time point of assessment^a^
Demographic data parents	Sex, age, country of birth, years in Sweden, level of education, housing conditions, employment, weight, height, number of children	T0
Child’s diet	Child Eating Habits Questionnaire EQ [73] Revised version of Eating and Physical Activity Questionnaire (EPAQ) [53] Mobile phone based photo method based on Delisle et al. [54]	T0, T1, T2
Child’s physical activity and sedentary behaviour	Accelerometry Questionnaire: Active transport, activity in organisation, screen time on week days and weekends	T0, T1, T2
Child’s sleep	Revised version of Eating and Physical Activity Questionnaire (EPAQ) [53]	T0, T1, T2
Child’s BMI	Height and weight measured with instruments (SECA)	T0, T1, T2
Child’s waist circumference	Measured with instruments (SECA)	T0, T1, T2
Parental self-efficacy	Revised instrument based on Wright et al. [63]	T0, (TM), T1, T2
Parental feeding practices	Comprehensive Feeding Practices Questionnaire [64]	T0, (TM), T1, T2
Parenting practices regarding children’s physical activity	Items derived from item bank by Masse et al. [65]	T0, (TM), T1, T2
Nurses’ self-reported MI competence	Revised version of self-rating questionnaire based on MITI 4 [49]	TM
Parent-report of nurse’s MI competence	Revised version of self-rating questionnaire based on MITI 4 [49]	TM

^a^T0: baseline; TM: between T0 and T1; T1: 6 months after baseline; T2: follow-up 18 months after baseline

#### Primary outcomes

The primary outcome is intake at home of a composite score of indicator foods of importance for energy-balance and health, namely fruit and vegetables (healthy foods) and unhealthy foods (sweets, ice cream, buns/cakes, crisps) and unhealthy drinks high in added sugar (sugar-sweetened beverages). Intake of indicator foods was chosen as the primary outcome because our previous studies in comparable population samples showed that diet was a discriminating factor between different socioeconomic and ethnic groups [6] and also improved as a result of the intervention [10, 12]. Intake will be assessed using food frequency questionnaire, the Children’s Eating Habits Questionnaire (CEQ) which measures intake retrospectively in the home during the preceding month, and shows good reliability [52]. This food frequency instrument has been specifically designed for parents of children aged 2–11 years in eight European countries including Sweden and aims to investigate dietary behaviour and the family food environment. In addition, a revised version of the Eating and Physical Activity Questionnaire (EPAQ) will be used [53]. It measures the child’s intake of indicator foods in the home environment during the previous week, and is a semi-quantitative food frequency questionnaire, and includes portion size both in written text and in pictures. The original EPAQ measured intake during the previous day only and was validated against a 24-h recall in an Australian setting with parents of two to five-year-old children [53]. We will also use a new smartphone-based method to estimate the intake of indicator foods eaten at home (volume and frequency) prospectively through standardised photos taken by parents over two weekdays and one weekend day. This method constitutes a further development of the method developed by Delisle et al. [54]. Newer technology-based methods show promise for improving the accuracy of food records [55]. A relative validation study will be conducted in parallel during baseline, where all methods will be compared to multiple 24-h recalls conducted by independent dietitians as the reference method. Our intention is to use the photo-based method for the primary outcome in the intervention study if shown to be valid. The EPAQ will be used for comparison with our previous studies [10, 12].

#### Secondary outcomes

Secondary outcomes are physical activity and time spent sedentary, which will be measured objectively using accelerometry (GT3X+, Actigraph, LCC, Pensacola, USA) over 7 consecutive days which is considered valid and reliable [56]. The accelerometers are worn on a belt at the right hip and the children are instructed to wear the monitors during waking hours and to remove them for activities involving water. Children with at least 500 min of activity registration per day for a minimum of 3 days, including at least one weekend day, will be included in the analyses. Non-wear time will be defined as 60 min of consecutive zeros allowing for 2 min of non-zero interruptions. The epoch length will be set to 5 s. Cut-points for sedentary intensity will be defined as all activity below 100 cpm, moderate to vigorous intensity will be defined as all activity above 2296 cpm, and vigorous intensity will be defined as all activity above 4012 cpm [57]. A questionnaire with the following items will also be used: Is your child active in a club? How many times a week does your child participate in club activities? How does your child usually travel to school? How long does the travel take? How many hours per day does your child spend at the computer, tablet, smartphone (hours) during week days/weekends? Body composition (height, weight and waist circumference) will be measured using standardised procedures using SECA instruments by trained assistants, to a level of precision of 1 mm for height and waist circumference, and 100 g for weight. Waist circumference will be measured over the umbilicus, with the child standing upright with arms alongside the body and after exhalation. BMI status will be defined according to the International Obesity Task Force [58]. BMI standard deviation score (BMI sds) will be calculated according to a Swedish reference standard [59] and according to International Obesity Task Force references [58]. One item from the EPAQ will be used to estimate sleeping hours in the children by parental report [53].

#### Covariates

Parental educational level and occupation is self-reported. Based on previous experience, we anticipate that a high proportion of parents will have a non-Swedish background and therefore a composite measurement of SEP is likely to be more appropriate. The composite measurement will consist of the highest level of education attained, and the occupation (according to Statistics Sweden) by either of the parents. A dichotomised variable indicating low and high SEP will be created. Parents will also be asked to indicate their country of birth as well as number of years living in Sweden. Country of birth will be classified as “Sweden/the Nordic region”, “Europe” or “outside Europe”. In addition, child sex will be used.

### Process evaluation

The process evaluation is based on the MRC guidance by Moore et al. [60]. The process evaluation will include intervention dose, fidelity, feasibility, acceptability and a description of the context.

#### Dose

The dose will be estimated quantitatively in the following way. Parents will be asked in a non-judgmental way by the school nurse if they have read the brochure. The number of MI sessions per family will be noted. Compliance with the teaching sessions and workbook completion will be monitored by teachers in a logbook, documenting core elements of the lesson, how much time they spent on each lesson, and whether they made any adaptations. The result of the T2D test will be available from the website.

#### Fidelity

Fidelity to the MI component will be assessed as follows. All MI sessions will be recorded and a random selection of 10–20% will then be coded for MI competence using the MITI protocol [49] by reliable coders in a coding lab at Karolinska Institutet (MIQA group). The MI competence of all nurses in the intervention and control group will be assessed before the first MI training in May 2017 by recording them having a standardised conversation with a trained actor posing as a parent. This will be repeated after MI training in August/September 2017, and again after the end of intervention in May 2018.

The school nurses in the intervention group will report the self-perceived MI quality of each MI session with parents. After each session the nurses will appraise their level of empathy they projected during the session, how much they focused on evoking change talk from the parents, and how much they used ‘reflections’ as opposed to posing questions. Parents will respond to an equivalent questionnaire after the MI session where they rate their perception of the school nurse’s expression of empathy and ability to motivate the parent to improve practices.

#### Feasibility and acceptability

After the end of the intervention, semi-structured interviews with parents, school nurses and head teachers will be performed to explore their views on the acceptability and feasibility of the intervention. In addition, focus groups will be conducted with the children to explore their perceptions of the activities in class and the home assignments. As an incentive to participate in the focus groups, children will receive a gift card to a book shop worth about 10 euro. Qualitative methods permit the researcher to study selected issues in depth and detail [61]. The interview guides will be based on the five interrelated domains of implementation (intervention characteristics, outer setting, inner setting, characteristics of the individuals involved, and the process of implementation) of the Consolidated Framework for Implementation Research (CFIR) [62]. This framework provides a pragmatic structure for analysing implementation factors in complex, multi-level interventions. Based on the findings, implementation strategies will be adjusted, if necessary, and a final manual will be produced after the end of the study.

#### Mediators

The potential mediators parental self-efficacy and observational learning/role modelling will be measured by questionnaires in both mothers and fathers. A revised and culturally adapted version of the 16-item questionnaire assessing parental self-efficacy regarding children’s diet and physical activity [63] will be used. The original instrument was validated in a sample of individuals mainly with low SEP and has been adapted by our research group to parents with a heterogeneous cultural background by changing the content and wording of some items. The instrument assesses parental self-efficacy for influencing physical activity during the weekend, intake of vegetables, sweets and chocolates, and sugar-sweetened beverages, each in three challenging situations. Parental feeding practices, including modelling, will be measured using the Comprehensive Feeding Practices Questionnaire (CFPQ) covering both positive and negative practices and validated in a middle-income US sample [64]. The questionnaire will assess the parental feeding practices of involvement, environment, food restriction for weight control, restriction for health reasons, encouragement of balance, pressure to eat, monitoring, emotion regulation, food as reward, and modelling. Few instruments exist to assess parenting practices regarding children’s physical activity and none of the existing ones show acceptable psychometric properties. Therefore, 25 items will be used from an item bank currently being developed for this purpose [65]. The items cover the parenting practices modelling, pressure, encouragement, guided choice, involvement/praise, co-participation, facilitation, monitoring, and restriction. All questionnaires have been translated into Swedish and back-translated by the research team and pre-tested in parents with pre-school children.

### Data management

All participants will receive a code and data will be depersonalised. The linking code will be kept separate from the data in a secure and locked place. Data collected during anthropometric measurements will first be written on paper and subsequently entered into the database by the research group. Original paper documentation will be saved and stored securely at Karolinska Institutet to allow for quality control of electronical data entry. Data collected though photos will be coded according to a standaridised operating procedure by dieticians/nutritionists and tested for inter-rater reliability on a regular basis. Data gathered using accelerometry will be analysed with the ActiLife software programme. Original data will be stored electronically.

All data collected through the project website and otherwise will be stored electronically in password protected folders on a secure data server at Karolinska Institutet to avoid unauthorized access. Folders containing raw data will be stored separately from the data being used in analysis. Measures to prevent loss of data will be taken through the use of systematic back-up routines throughout data collection and by data storage on servers with complete data back-up on a daily basis. Access to data will be restricted to the research personnel working directly with data entry or analyses.

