### Study design

The Healthy School Start Plus study will be conducted as a cluster-randomised parallel trial with randomisation at school level, with a wait-list control group. Simple randomisation of schools to the intervention or control group with a 1:1 allocation ratio was done using a computer-generated randomisation procedure by a statistician not involved in the study. As all school nurses in the intervention group had to undergo training in Motivational Interviewing (MI), something that takes a few months to reach a certain level of competence, randomisation took place before the baseline measurements in order to allow time for this training. However, allocation of schools to intervention or control was only revealed to headmasters, school nurses and the project leader, until baseline measurements done by research assistants, were finalised. Only then were teachers and parents informed. Baseline data was collected in September–October 2017 (T0) from 352 children. Data will again be collected 6 months after the baseline at the end of the intervention in April–May 2018 (T1) and at follow-up in April–May 2019 (18 months post baseline, T2). As an incentive to retain participants in the study, each family will receive a coupon for a healthy meal at a shopping centre restaurant. Mediators will also be measured on one occasion during the intervention, in February 2018 (TM). After the T2 measurement the control schools will be offered the intervention, including MI-training of the school nurses.

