Mediation analysis will be performed according to MacKinnon [66] with parental self-efficacy and parenting practices, including modelling, as the hypothetical mediators, to see if the programme works according to its theory, and whether effects are moderated by child sex or SEP. All statistical analysis will be performed blinded to group allocation.

Interviews and focus groups will be transcribed verbatim and analysed using qualitative content analysis [67].

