Another weakness is that we had to randomise schools to intervention and control groups before the baseline measurement was performed. This was necessary as nurses in intervention schools had to undergo a training period and because the intervention had to follow the school year. However, we did our best to keep intervention allocation hidden from other school staff and research assistants until baseline measurements were finalised. For obvious reasons, blinding of participants, nurses, teachers and the research team was not possible after the intervention had started which could lead to biased responses and differential response rates among participants. However the data analysis will be performed blinded to group allocation.

Mixed-methods will be used in the study to evaluate the implementation process. Qualitative methods permit the researcher to study selected issues in depth and detail, such as e.g. positive and negative views held by participants regarding the intervention and possible unwanted effects. Mixed methods are recommended when conducting pragmatic (real-world) trials, because they can reveal if a potential lack of effect is caused by intervention failure or implementation failure or both. In agreement with the UN Convention on the Rights of the Child we will interview the children about their experience and perception of this intervention.

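### The protocol declares research-team blinding impossible after baseline and does not exempt the photo coders, although masking those who code the intended primary outcome is feasible and cheap

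*Protocol article*

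**What the plan says.** All places are in the protocol article.

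- **Discussion:** the limitations paragraph says that "blinding of participants, nurses, teachers and the research team was not possible after the intervention had started". It names biased answers and unequal response between arms as the resulting risks, both on the participants' side, and offers blinded data analysis as the safeguard.
- **Data analysis:** "All statistical analysis will be performed blinded to group allocation".
- **Study design:** before follow-up, "allocation of schools to intervention or control was only revealed to headmasters, school nurses and the project leader, until baseline measurements" were complete. The Discussion adds that "we did our best to keep intervention allocation hidden from other school staff and research assistants until baseline measurements were finalised". Masking of the assistants is therefore described up to the end of baseline only.
- **Primary outcomes:** "Our intention is to use the photo-based method for the primary outcome in the intervention study if shown to be valid". The photos are taken by parents and used to estimate volume and frequency of indicator foods. The Discussion names a questionnaire as backup.
- **Data management:** the photos "will be coded according to a standaridised operating procedure by dieticians/nutritionists and tested for inter-rater reliability on a regular basis". The same section gives participants a code and stores the linking key separately, as part of data protection.
- **Secondary outcomes:** body measurements are taken "by trained assistants, to a level of precision of 1 mm for height and waist circumference". Nothing is said about masking at T1 or T2.

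**The concern.** The Discussion takes a position on the research team as a whole, exempting only the analysis. That is broader than its reason supports. Parents, nurses and teachers cannot be masked because they receive or deliver the programme. A dietician estimating portions from an image after the event does neither.

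Estimating volume from a photo involves judgement, so knowledge of the arm can shift it. The two safeguards on offer do not address this. Inter-rater agreement measures consistency, and coders with the same knowledge can agree closely while all leaning the same way. Blinded analysis starts from values already coded. Adjustment for baseline does not help either: a shift that enters only at follow-up goes straight into the adjusted difference between arms.

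At stake is the measure intended to improve on self-report, which the protocol calls its main weakness.

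**Working it through.** **1. What the text settles.**

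| Role | Masking stated up to end of baseline | Masking stated afterwards |
|---|---|---|
| Research assistants | Yes, attempted | None; research team declared unblindable |
| Photo coders | Not stated | Not stated; no exemption from the Discussion sentence |
| Data analysis | n/a | Yes |

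The point therefore rests on a stated position that is too broad, together with a coding description that makes no exception to it. It does not rest on silence alone.

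**2. The plan's own sample size.** Inputs from Sample size calculation: SD 2.0, difference 0.8 portions/day, power 80%, alpha 5% (taken as two-sided), ICC 0.02, 15 children per school.

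- Per arm without clustering: 2 × (1.960 + 0.842)² × 2.0² / 0.8² = 98.1, rounded up to 99; total 198.
- Design effect: 1 + (15 − 1) × 0.02 = 1.28.
- 198 × 1.28 = 253.4 children; 253.4 / 15 = 16.9 schools, so 17 × 15 = 255.

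The stated 255 reproduces, and masking coders does not change it.

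**3. Standard error of the arm difference**, taking equal arms:

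- 255 children: 2.0 × √(1.28 × 2 / 127.5) = 0.283 portions/day.
- 352 children (the baseline number): mean school size 352 / 17 = 20.7; design effect 1 + 19.7 × 0.02 = 1.394; SE = 2.0 × √(1.394 × 2 / 176) = 0.252.

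**4. Type I error under an assumed coding shift b between arms, with no true effect:** Φ(−1.96 + b/SE) + Φ(−1.96 − b/SE).

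| Assumed b (portions/day) | Share of 0.8 | 255 children | 352 children |
|---|---|---|---|
| 0 | 0% | 5.0% | 5.0% |
| 0.1 | 12.5% | 6.4% | 6.8% |
| 0.2 | 25% | 10.9% | 12.5% |
| 0.3 | 37.5% | 18.5% | 22.2% |

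For example, with b = 0.2 and 255 children, b/SE = 0.706, and Φ(−1.254) + Φ(−2.666) = 0.105 + 0.004 = 0.109.

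**5. Limits of step 4.** The documents give no coding error, so b is an assumption. The SD comes from the group's previous study. The EPAQ is kept for comparison with earlier studies, which suggests a questionnaire-based SD and not one from a three-day photo record. The SE ignores baseline adjustment, which would lower it and raise the inflation for a given b, and attrition, which would do the opposite.

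**The case against.** The strongest reply is that no sentence says the coders know the arm. The dieticians/nutritionists are not expressly placed in the research team, the Discussion sentence is a general limitation, and the operating procedure, which is not shown and could require masking, belongs to a fuller document than a journal article. Participant codes with a separate linking key may hide the arm in practice.

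Part of this stands. A reader might infer that coders are known to be unmasked, or that participant codes reveal the school. The documents support neither. What remains is that the article declares the research team unblindable, exempts only the analysis, and presents the codes as confidentiality and not as masking. If coders are in fact masked, one sentence would show it, and the Discussion sentence would still need correcting.

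A second stronger reading is that masked baseline work proves T1/T2 body measurements can be masked with no extra staff. It does not. At T0 teachers and parents were also unaware and nothing had been delivered. By T1 classes have had the sessions and parents have been offered Motivational Interviewing. Assistants may have learned the allocation since baseline, and anyone at the visit could disclose it. Height and weight are instrument readings under a standard procedure, which leaves little room for bias; waist leaves somewhat more.

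It is also fair that unblinded parents take the photos, so what they choose to serve or record can still differ by arm whoever does the coding.

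**Conclusion.** The point holds for photo coding. The protocol's statement on blinding is too broad, and it leaves an avoidable source of detection bias open in the intended primary measure.

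Its size is unknown. The table shows what a shift would do if it occurred: at 255 children, between 6.4% and 18.5% type I error for assumed shifts of 0.1 to 0.3 portions/day. A reader might take these as the trial's actual error rate. They are not, because both the shift and the applicability of the SD to photo data are assumptions.

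The benefit has two limits. Masking coders removes only the assessor's share of the bias. It also matters for the primary outcome only if the photo method is validated and adopted; under the questionnaire backup it would not help. For body measurements the case is weaker and supports only a where-feasible recommendation.

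**What to change.** 1. In Data management, state that photo coders are not told the allocation and that images reach them under a neutral ID without school or arm.
2. Code T1 and T2 images from both arms in mixed batches. T0 images needed for the validation study may be coded earlier, also mixed across arms.
3. In the Discussion, limit the statement that blinding was impossible to those for whom the reason holds, and say that photo coding is masked.
4. For T1/T2 body measurements, where existing staff allow, use assistants who have not been told the allocation, and record any unmasking.

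The cost is relabelling files and organising batches. Sample size and analysis are unchanged. Item 4 may not be achievable everywhere and should not hold up items 1 to 3.
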